### Secondary outcome measures

The numbers of exacerbations will be analysed in Poisson-type regression models, with the time spent in the study as offset, thus adjusting for potential loss to follow-up. The other secondary outcome measures, that is, generic quality of life (measured by CHU9D and EQ-5D), disease-specific quality of life (PAQLQ), satisfaction and 3-monthly costs will be analysed in separate multilevel regression models. The probability of achieving asthma control at any moment in time will be analysed in a multilevel logistic regression model. Asthma control is defined as a C-ACT score of 20 or better.

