## Methods/design

### Design

The aim is to conduct a cluster RCT with a follow-up of 18 months. Recruited practice nurses (or groups of practice nurses) representing one cluster will be randomised into one of the two arms: (1) protocolled nurse-led care or (2) ‘usual care’ by the GP. During the study, a number of potential participating GPs were already intending to start protocolled nurse-led care for children with asthma in their practice. Because of this reason, we decided to enable these health centres to participate in the non-randomised part of the trial. This new sample was added after the study started and the change was approved by the ethics committee. All measurements and study procedures (except for the randomisation) will be identical to the randomised group of patients. Figure 1 is a flowchart of the study design.

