### Baseline measurements and questionnaires

Height and weight, asthma, control according to GINA guidelines, ethnicity of the child, smoking status of the parents and smoking status of the mother during pregnancy will be determined during the baseline visit by the practice nurse. All these items are entered in an online data management system with a secured ‘cloud’ (Research Manager, Deventer, the Netherlands).

The other questionnaires: the C-ACT, CHU9D, EQ-5D-Y, the questionnaire on satisfaction with delivered care, the questionnaire on the frequency/severity of exacerbations and on healthcare costs will be sent to the parents (digitally) at baseline and at 3, 6, 12 and 18 months. The PAQLQ questionnaire will be sent to the parents only at baseline and at 6 and 18 months.

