### Primary outcome measures

C-ACT scores will be analysed in a multilevel repeated measures regression model, which incorporates the C-ACT scores for all measurements, including the baseline measurement. This method takes into account within-patient correlation by modelling the covariance structures of the residuals per measurement. Several structures will be considered, starting with the unstructured covariance structure.

The differences in C-ACT scores between the two groups will be modelled by the interaction of treatment and measurement after baseline, assuming that any difference in C-ACT at baseline is due to chance. Additional variables will be considered for inclusion in the regression model if they are substantially different at baseline or if they are expected to be predictive of drop-out at a later stage.

Furthermore, a subgroup analysis will be conducted in which the total sample is divided into three groups according to their baseline characteristics; a group with insufficient asthma control (undertreated children), a group with sufficient asthma control and continuous ICS use (possible overtreated children) use and a group with the remaining children.

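### The exacerbation model names no baseline term although a baseline exacerbation report is collected; prespecifying it is a cheap improvement whose gain may be small

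*Protocol article*

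**What the plan says.** In the protocol article, the Secondary outcome measures section under Analyses gives the exacerbation model in one sentence: "The numbers of exacerbations will be analysed in Poisson-type regression models, with the time spent in the study as offset". The stated purpose of the offset is to allow for loss to follow-up. No covariate is named for this model or for the other secondary models in that section.

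Baseline measurements and questionnaires shows that a pre-treatment report is planned: "the questionnaire on the frequency/severity of exacerbations and on healthcare costs" is among the forms that "will be sent to the parents (digitally) at baseline and at 3, 6, 12 and 18 months". The recall period of this form is not given.

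For the primary outcome, the Primary outcome measures section under Analyses is more specific. The C-ACT model "incorporates the C-ACT scores for all measurements, including the baseline measurement". The same section has the article's only covariate rule: "Additional variables will be considered for inclusion in the regression model if they are substantially different at baseline", or if they are expected to predict drop-out. Neither provision is extended to exacerbations.

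**The concern.** Children differ in how prone they are to exacerbations, and an earlier count carries information about a later one. The entry criteria are wide enough to make such differences plausible: they run from a single bronchodilator prescription with a diagnostic code to children on inhaled corticosteroids. Allocation is by cluster. The Setting section describes 13 health centres and at least 14 smaller practices, and Randomisation stratifies on practice size and GP experience, not on exacerbation history. The Discussion itself recognises that baseline imbalance is possible in such a design.

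At stake are the precision of the rate ratio for a named secondary outcome and how far that single estimate is moved by the mix of children each arm happens to receive. The Sample size section powers the trial on C-ACT alone, so precision for exacerbations is not secured elsewhere.

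**Working it through.** The plan states no rate, rate ratio, dispersion or power for exacerbations, so there is no figure of its own to reproduce.

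**Inputs from the article.** Follow-up T = 1.5 years (Design). 180 children and 15% loss (Sample size), hence 180 × 0.85 = 153 with follow-up.

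**Assumed inputs.** Rate L = 0.5 or 1 exacerbation per year; between-child dispersion k = 1 (gamma-Poisson counts); baseline recall window B = 4 weeks, 3 months or 12 months.

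**Formula.** Without the baseline count, the variance of the log rate ratio is proportional to 1 + kLT. Using the baseline count reduces the dispersion to about k/(1 + kLB). So

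variance ratio (adjusted / unadjusted) = [1 + kLT/(1 + kLB)] / (1 + kLT).

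This equals 1 − ρ², where ρ is the correlation between baseline and follow-up counts.

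- L = 0.5, 3 months: (1 + 0.75/1.125)/1.75 = 1.667/1.75 = 0.952.
- L = 0.5, 12 months: (1 + 0.75/1.5)/1.75 = 1.5/1.75 = 0.857.
- L = 1, 12 months: (1 + 1.5/2)/2.5 = 1.75/2.5 = 0.70.

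**Simulation check.** 1000 runs, 153 children in 27 clusters (13 + 14, taking each centre or practice as one cluster), no treatment effect, no cluster effect, negative binomial regression with and without log(1 + count).

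| L per year | Recall | Ratio, formula | Ratio, simulation | Shift in unadjusted rate ratio per 1-SD imbalance | Same, adjusted |
|---|---|---|---|---|---|
| 0.5 | 4 weeks | 0.984 | 1.005 | 4.3% | 1.1% |
| 0.5 | 3 months | 0.952 | 0.968 | 6.5% | 0.5% |
| 0.5 | 12 months | 0.857 | 0.929 | 9.8% | −0.1% |
| 1 | 4 weeks | 0.957 | not run | | |
| 1 | 3 months | 0.88 | 0.964 | 8.0% | −0.1% |
| 1 | 12 months | 0.70 | 0.85 | 10.7% | −0.6% |

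The simple covariate achieved less than the formula. With 12-month recall the cut is 14% to 30% by formula and 7% to 15% by simulation. With 4-week recall it is 2% to 4% by formula and nil in the one case simulated. With k = 0 the formula gives no gain at all.

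**Effect on the interval** (simulated SDs of the log rate ratio, 12-month recall). At L = 0.5 the SD falls from 0.249 to 0.240, so the 95% limits lie a factor exp(1.96 × 0.249) = 1.63 from the estimate without adjustment and exp(1.96 × 0.240) = 1.60 with it. At L = 1 the SD falls from 0.207 to 0.190 and the factor from 1.50 to 1.45.

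**Centring.** The mean log rate ratio lay between −0.012 and 0.009 for both estimators in every scenario, that is, a rate ratio of about 1.00.

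**The case against.** The strongest reply is that silence is not exclusion. This is a condensed article, its secondary models are given in a sentence or two each, and the covariate list of such a model is commonly left to the analysis plan. That stands. A reader might infer that the plan rules out baseline adjustment, or that it contradicts the C-ACT model. It does neither: no sentence says the exacerbation model is unadjusted, and a detailed primary model beside a brief secondary one is not an inconsistency. What remains is a suggestion about the model as stated. If the covariate rule for C-ACT were carried over, adjustment would depend on the imbalance seen, which is weaker than naming the term in advance.

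A reader might also infer that an arm with more exacerbation-prone children would show a spurious treatment effect, in other words bias. The documents do not support that reading for chance imbalance. The unadjusted rate ratio is correctly centred over repeated randomisations, and an interval that handles overdispersion and clustering already allows for such imbalance. The Discussion also points to stratification as its remedy, though the strata do not address exacerbation history directly.

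Thirdly, the baseline form may not always precede knowledge of the arm. The trial is open-label, Randomisation provides for further patients in a cluster already allocated, and the article does not say that the form is completed before parents are told. A parent report given after disclosure could be affected by it. This is a fair caveat and shapes the fix, but does not remove it.

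**Conclusion.** The point holds as a low-severity improvement. A baseline exacerbation report is planned, the stated model names no term for it, and using it would recover some precision and take most of the chance imbalance in that count out of the reported estimate.

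The size rests wholly on assumed rates, dispersion and recall. At 0.5 to 1 exacerbations per year and dispersion 1, the variance cut runs from near 0% with 4-week recall to about 7% to 30% with 12-month recall, where 7% is the simulated figure at the lower rate and 30% the formula figure at the higher. The simulation had no cluster effect.

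A reader might be tempted to claim a large gain in power by assuming a baseline to follow-up correlation of 0.5, which gives 1 − 0.5² = 0.75, a 25% cut. In the model used here that is close to the most favourable case in the table (12-month recall at 1 per year, ρ² = 0.30). With 4-week recall at 0.5 per year, ρ² is only about 0.016. The documents give no means of choosing between these.

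**What to change.** Add a sentence to the Secondary outcome measures section under Analyses. It should name the child's baseline exacerbation count, for example as log(count + 0.5), as a covariate in the Poisson-type model, regardless of any imbalance observed. It should also state:

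- the recall window of the baseline form;
- that only reports completed before the family learns the allocation are used;
- a simple rule for children without such a report, for example a missing-form indicator, with their number given by arm, since for children recruited after their cluster was allocated the absence of a usable report may itself be related to the arm.

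The cost is a line of text and one extra parameter (two with the indicator). No new data, visits or children are needed. The gain may be small if the recall window proves short.

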### Secondary outcome measures

C-ACT outcomes at 3, 6, 12 and 18 months.Frequency and severity of exacerbations. Exacerbations of asthma are episodes characterised by a progressive increase in asthma symptoms, that is, they represent a change from the patient’s usual status that is sufficient to require a change in treatment. This will be determined by a questionnaire filled out by the parents.Generic health-related quality of life at 3, 6, 12 and 18 months. This will be measured by the Child Health Utility 9D (CHU9D)^28^ and the EuroQol 5D-5L-Y (EQ-5D-Y).^29^ Both instruments were specifically designed for use in children.Direct and indirect healthcare costs. The parents will be asked to record healthcare resource use and absence from paid work in diaries. Hospital costs will be assessed by a retrospective chart review at 18 months and by a questionnaire to the parents of the patients.Cost-effectiveness and cost-utility.Disease-specific quality of life measured by the Standardised Paediatric Asthma Quality of Life Questionnaire (PAQLQ(S)) at baseline and at 6 and 18 months.^30^
Patient/parent/nurse/GP satisfaction with delivered care. The questionnaire consists of one statement: ‘Overall, I am satisfied with current asthma care by my GP practice’. The Likert scale will be as follows: strongly disagree, somewhat disagree, neither agree nor disagree, somewhat agree, or strongly agree.Spirometry: forced expiratory volume in 1 s (FEV1), forced expiratory flow at 75% of vital capacity (FEF 75) and reversibility at baseline and at t=18 months.Medication use in the intervention and control group, measured by a questionnaire.

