### Retrospective chart review

Direct and indirect healthcare costs and information on co-morbidity will be assessed at 18 months by retrospective chart review. In the Netherlands, all hospital visits (both emergency room visits and cases that are admitted to stay in hospital) are reported to the GP; this includes the duration of stay. The following items will be assessed: referrals from primary to secondary care, number of hospital admissions, medication costs, number and duration of consultations and consultations with the practice nurse and/or the physician (for asthma and non-asthma related symptoms), evidence of stepping-down therapy (ie, reduction in prescribed medication) and information on allergies.

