### Missing data

The multilevel regression model also deals with missing observations of the outcome measure by exploiting the fact that observations within patients are correlated, if the missingness occurs completely at random or at random (conditional on the observed data in the model). This allows unbiased estimation of regression coefficients and to make optimal use of all available data, even when some measurements are missing.^32^ Dropouts or missing visits will be reviewed to identify possible informative missingness.

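### The exacerbation model takes time in the study as exposure, although events are known only from returned parent questionnaires, so enrolled time that no returned form covers counts as event-free

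*Protocol article*

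**What the plan says.** Three parts of the protocol article bear on this.

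- **Source of the events.** Under Methods/design, Secondary outcome measures, an exacerbation is a worsening of symptoms; such episodes, it says, "they represent a change from the patient’s usual status that is sufficient to require a change in treatment". On how they are ascertained: "This will be determined by a questionnaire filled out by the parents". Under Baseline measurements and questionnaires, the exacerbation form is among those that "will be sent to the parents (digitally) at baseline and at 3, 6, 12 and 18 months". The recall period of this form is not given.
- **Analysis.** Under Analyses, Secondary outcome measures, the counts go into a Poisson-type model. The exposure term and the reason for it are given there as follows: "with the time spent in the study as offset, thus adjusting for potential loss to follow-up".
- **Other relevant text.** The Retrospective chart review at 18 months covers items such as "referrals from primary to secondary care, number of hospital admissions, medication costs, number and duration of consultations", but does not list exacerbations. The Missing data section begins: "The multilevel regression model also deals with missing observations of the outcome measure". It ends with a general promise to look into dropouts and missed visits for informative missingness. Neither section says how exposure is counted for a child who stays in the trial but does not return an exacerbation form.

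**The concern.** In a rate model, the offset should be the time during which an event, had it happened, would have been counted. Here an event can be counted only if a parent returns a form whose recall period includes it. Time in the study is a different quantity. The two agree only if reporting is complete up to the moment the child leaves. The article justifies the offset as an adjustment for loss to follow-up. That deals with time after leaving, but not with gaps in reporting before it.

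Such gaps are foreseeable. Under Withdrawal of individual participants, a child leaves by choice or by the investigator's decision on medical grounds; not answering forms is not mentioned. Home spirometry and chart review are planned at 18 months and do not depend on which forms came back. A child can therefore remain enrolled with forms missing.

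Two things are at stake. Exacerbation rates in both arms would be understated. If the uncovered share of time also differs between the arms, the rate ratio would be distorted.

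**Working it through.** The article states no exacerbation rate, power or return rate, so it offers no figure to reproduce. The check is of the exposure rule itself.

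**Inputs from the article.** Follow-up is 18 months. Forms at 3, 6, 12 and 18 months give intervals of 3, 3, 6 and 6 months. Expected loss to follow-up is 15% (Sample size).

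**Assumptions.** Uncovered shares of time, q, by arm; a true rate of 0.5 per year (simulation only); non-return unrelated to exacerbations.

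**Step 1: one missed form.** For a child followed for 18 months, if no later form covers the gap:

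- form at month 3 or 6: 3/18 = 16.7% of the offset has no recordable event;
- form at month 12 or 18: 6/18 = 33.3%.

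**Step 2: effect on a rate.** With true rate λ, in-study time T and uncovered share q, expected recorded events are λT(1 − q). Dividing by T gives λ(1 − q). At λ = 0.50 per year, q = 10% gives 0.50 × 0.90 = 0.45, and q = 20% gives 0.50 × 0.80 = 0.40.

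**Step 3: effect on the rate ratio.** The true ratio is multiplied by (1 − q_int)/(1 − q_usual):

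| q, nurse-led | q, usual care | Multiplier |
|---|---|---|
| equal | equal | 1.000 |
| 10% | 20% | 0.90/0.80 = 1.125 |
| 10% | 30% | 0.90/0.70 = 1.286 |
| 20% | 10% | 0.80/0.90 = 0.889 |

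The direction depends on which arm reports less completely.

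**Step 4: simulation.** Set-up: 90 children per arm, 15% dropout, intervals of 3/3/6/6 months, true ratio 1, 1,500 replicates. Skipped forms are not recovered.

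| Non-return, usual care / nurse-led | Rates per year with study-time offset | Ratio | Ratio with covered-time offset |
|---|---|---|---|
| 0% / 0% (dropout only) | 0.499 / 0.502 | 1.005 | 1.005 |
| 10% / 10% | 0.451 / 0.452 | 1.002 | 1.002 |
| 20% / 20% | 0.400 / 0.401 | 1.003 | 1.003 |
| 20% / 10% | 0.403 / 0.447 | 1.107 | 0.983 |
| 30% / 10% | 0.352 / 0.450 | 1.279 | 0.996 |
| 10% / 20% | 0.446 / 0.401 | 0.899 | 1.009 |

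The simulation agrees with Step 3 once its sampling noise is removed: 0.983 × 1.125 = 1.106, against 1.107. The first row shows that dropout alone does no harm under the stated offset. With covered time as offset, every scenario returns a rate of about 0.50 per year and a ratio of about 1.

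**Step 5: dependence on the recall period.**

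- If each form asks about the time since the last completed form, a skipped middle form is recovered when a later one is returned. A run of missing forms at the end is not.
- If each form asks only about its own interval, a skipped form is lost.
- If recall is shorter than the 3- or 6-month gap, time in the study exceeds covered time even when every form is returned.

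**The case against.** The strongest reply is that the article does not define time in the study. Because the offset is meant to handle loss to follow-up, and a family that stops answering is an ordinary case of such loss, one could take it to run only to the last returned form. Trailing non-response would then cause no error, and a condensed article may leave the derivation to a fuller document. This limits how firmly the trailing case can be stated. It does not remove the point. The article chose an offset and gave a reason for it, and that reason does not cover a form skipped in the middle or a recall window shorter than its interval.

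Three stronger readings are tempting, and the article does not support them.

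- **Every unreturned interval counts as event-free.** Time after exit is outside the offset, and a later form may recover a skipped interval, depending on the unstated recall period.
- **The treatment comparison is biased.** That needs unequal uncovered shares or, beyond the formula used here, non-return that depends on exacerbations differently by arm. The trial is open-label, and visits can be as frequent as every 2–4 weeks for poorly controlled children in the nurse-led arm, against the GP's discretion in usual care, so unequal return is plausible. But the forms are digital and the article describes one schedule for both arms. Well-controlled children in the nurse-led arm who were diagnosed more than a year ago are seen only annually. No return rates are given.
- **The 15% loss measures the problem.** It is an allowance for loss to follow-up, not for non-response while enrolled.

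The closing sentence of Missing data, on reviewing dropouts and missed visits, is not confined to C-ACT. It promises a review, however, and does not change the exposure used in the count model.

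**Conclusion.** The point holds in a limited form. The numerator comes from returned forms and the stated denominator is time in the study. Enrolled time that no returned form covers is therefore treated as event-free, and the stated justification does not address it. The size is 17% or 33% of a fully followed child's exposure for each unrecovered form. Absolute rates are too low by the uncovered share. The rate ratio is unbiased if that share is equal in the two arms and is multiplied by 1.125 at 10% against 20%.

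The per-form shares follow from the article's own schedule, provided no later form fills the gap. The rate-ratio figures rest on assumed shares and on non-return being unrelated to exacerbations. If families fail to answer because of an exacerbation, a covered-time offset does not remove that bias either. The primary C-ACT analysis is not affected.

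**What to change.** In Analyses, Secondary outcome measures, define the offset as the person-time covered by the recall windows of the returned exacerbation questionnaires, and state the recall period. Each form's window should match the period it actually asks about, reaching back to the last completed form if it is worded that way.

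Fixed exposures of 3, 3, 6 and 6 months should not be used regardless of wording. If recall runs to the last completed form, a child who skips month 12 and answers at month 18 reports 12 months of events, which would be set against 6 months of exposure and overstate the rate.

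Chart-review admissions may serve as a separate sensitivity analysis of admission-level exacerbations, in both arms over full follow-up. They should not be used to fill unreturned intervals, because the article's definition of an exacerbation is broader than admission and milder events would still be missed.

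The cost is a sentence or two of text and one derived exposure variable, with no new data collection. Rates become slightly less precise because uncovered time no longer counts.

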### Economic evaluation

A prospective economic evaluation will be performed from both a healthcare perspective and a societal perspective alongside the clinical trial, according to Dutch and international guidelines.^33 34^ If nurse-led asthma care leads to more costs, as well as health gains compared with usual care, the cost-effectiveness will be expressed in the following incremental cost-effectiveness ratios (ICERs):

Costs per quality-adjusted life year (QALY).Costs per additional patient with asthma control.

The uncertainty around the estimates of incremental costs and effects, and around the ICERs, will be displayed on cost-effective planes and in cost-effectiveness acceptability curves.

Costs are calculated by measuring all relevant cost categories per interval at the patient level and multiplying natural units by standard prices. The costs are then analysed in a multilevel repeated measures regression model. Based on the regression results, adjusted average costs per interval and for the total study period are calculated for each treatment option. The healthcare perspective includes all medical costs (GP and nurse contacts, hospital admissions, pulmonologist or paediatrician consultations, medication). The societal perspective also includes the costs of parent’s production losses as a consequence of their child’s asthma.

The QALY calculations are based on the results of the regression analysis of the generic quality-of-life measurements (EQ-5D-Y and CHU-9D). The results are used to calculate adjusted average quality of life at the end of each interval for each treatment. After this, QALYs per interval can be calculated by taking the average of two measurements around the interval and multiplying this by the duration.

The results of a multilevel logistic regression analysis will be used to calculate individual and average probabilities of achieving asthma control at t=18 for each treatment. The costs per additional patient with asthma control can then be calculated as the ratio of the incremental costs and the difference of the average probabilities.

